### 3.2.2 Measures to control bias

To avoid possible bias, a double-blind placebo-controlled design is used in the study. At the same time, objective measurements are used for safety and efficacy endpoints which is hardly lead to bias.

### 3.2.3 Discontinuation Criteria

**If any of the following criteria are met, the investigator and the sponsor should immediately initiate a discussion procedure to decide whether to terminate the dose escalation in each cohort.**

- Occurrence of at least one serious treatment-emergent adverse event related to IBI362 (except for expected adverse events related to the pharmacological properties of IBI362, such as hypoglycemia, etc.).
- No less than 4 patients experience symptomatic hypoglycemic events (plasma glucose levels < 3.0 mmol/L) at a specific dose level, and those events are considered to be related to IBI362.
- No less than 2 patients receiving IBI362 experience persistent (more than one week) symptoms of acute pancreatitis.
- No less than 2 patients experience severe IBI362-related, non-serious adverse events at the same dose, regardless of whether the event is associated with the same organ or system.

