|                           | 
Cohort 2: Patients randomized to IBI362 or placebo initiate treatment with 1.5 mg once-weekly with dose escalations every 4 weeks by 1.5 mg until the maintenance dose (4.5 mg) will be achieved.
 
If 3.0 mg or 4.5 mg is not tolerated in Cohort 2, the dose should be adjusted according to the criteria in Table 1.
 
Cohort 3: Dosing should not be started until the patients in Cohort 2 complete the 4-week tolerability evaluation of 1.5 mg. If 1.5 mg is not well-tolerated, 2.0 mg and higher doses in Cohort 3 will not be explored. Patients randomized to IBI362 or placebo initiate treatment with 2.0 mg once-weekly with dose escalations every 4 weeks by 2.0 mg until the maintenance dose (6.0 mg) will be achieved.
 
The study will consist of a 3-week screening period, a 12-week double-blind treatment period, and an 8-week follow-up period.
 
Discontinuation Criteria: If any of the following criteria are met, the investigator and the sponsor should immediately initiate a discussion to decide whether to terminate dose escalation.
 
 
• Occurrence of at least one serious treatment-emergent adverse event related to IBI362 (except for expected adverse events related to the pharmacological properties of IBI362, such as hypoglycemia, etc.).
 
• No less than 4 patients experience symptomatic hypoglycemic events (plasma glucose levels < 3.0 mmol/L) at a specific dose level, and those events are considered to be related to IBI362.
 
• No less than 2 patients receiving IBI362 experience persistent (more than one week) symptoms of acute pancreatitis.
 
• No less than 2 patients experience severe IBI362-related, non-serious adverse events at the same dose, regardless of whether the event is associated with the same organ or system.
 
 |

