### 2.2 Study Endpoints

#### 2.2.1 Primary endpoint

- **Safety and tolerability:** During dose escalation, the incidence and severity of adverse events at each dose level, including chief complaint, physical examination, laboratory tests (hematology, blood chemistry, lipid panel, coagulation function, urinalysis, myocardial enzymes, serum amylase and/or lipase, thyroid function, calcitonin, etc.), vital signs (pulse, respiration, blood pressure, body temperature), 12-lead ECG and other examinations; treatment compliance; and record the name, clinical characteristics, severity, start and stop time, supportive care and outcomes of adverse events, correlation with the study drugs;

- **Maximum tolerated dose:** If the dose exploration is stopped when the criteria for stopping dose escalation are met at a certain dose level, the previous dose is the maximum tolerated dose. If the criteria are still not met when the maximum exploratory dose is reached, the maximum tolerated dose is greater than or equal to the maximum escalation dose.

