### 8.3.4 Hypoglycemic Events

Hypoglycemia is classified by severity as follows:

- **Severe hypoglycaemia:** refers to a condition where the patient requires the assistance of another person to obtain carbohydrate, glucagon or other rescue measures. Hypoglycaemic episodes may be accompanied by neuroglycaemic symptoms and, in severe cases, precipitate epileptiform convulsions or coma. Such events may not have been documented by blood glucose measurements, but recovery of neurological symptoms as blood glucose returned to normal is sufficient evidence that the event is caused by hypoglycemia.
- **Documented symptomatic hypoglycemia:** typical symptoms of hypoglycemia with a plasma glucose concentration less than or equal to 70 mg/dL (3.9 mmol/L).
- **Asymptomatic hypoglycaemia:** Asymptomatic hypoglycaemia are not shown with typical symptoms, but with a plasma glucose concentration less than or equal to 70 mg/dL (3.9 mmol/L).
- **Probable symptomatic hypoglycemia:** during the study, the symptoms of hypoglycemia are not accompanied by a plasma glucose determination, but symptoms are presumed to be caused by a plasma glucose concentration less than or equal to 70 mg/dL (3.9 mmol/L).
- **Relative hypoglycaemia:** The typical clinical symptoms of hypoglycaemia reported by a person with diabetes mellitus who considers himself/herself suffering from hypoglycaemia but with a measured blood glucose concentration greater than 70 mg/dL (3.9 mmol/L).

**The investigator will determine whether a hypoglycaemic episode is severe or not based on the need for medical assistance in addition to the intended assistance that the patient normally receives. All hypoglycaemic episodes will be recorded in the hypoglycaemic module of the eCRF and all severe hypoglycaemic episodes must be reported as SAEs.**

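### A severe IBI362-related hypoglycaemic episode can itself count only toward the four-patient stopping criterion, so fewer cases, or cases without a glucose value below 3.0 mmol/L, require no cohort-level discussion and leave the MTD statement unchanged

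*Combined protocol and SAP*

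**What the plan says.** Protocol 3.2.3, repeated in the synopsis, lists four criteria. Meeting any one obliges an immediate investigator–sponsor discussion on whether to end escalation. It does not stop escalation automatically.

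- Criterion 1: "Occurrence of at least one serious treatment-emergent adverse event related to IBI362", with the exemption "except for expected adverse events related to the pharmacological properties of IBI362, such as hypoglycemia, etc".
- Criterion 2: "No less than 4 patients experience symptomatic hypoglycemic events (plasma glucose levels < 3.0 mmol/L) at a specific dose level", the events being judged related to IBI362.
- Criterion 3: at least 2 IBI362 patients with pancreatitis symptoms lasting more than a week.
- Criterion 4: "No less than 2 patients experience severe IBI362-related, non-serious adverse events at the same dose".

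Protocol 8.3.4 defines severe hypoglycaemia by the need for another person's help. It says of these episodes: "Such events may not have been documented by blood glucose measurements". It also requires that "all severe hypoglycaemic episodes must be reported as SAEs".

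Protocol 2.2.1 makes the MTD a primary endpoint and reads it from the stopping criteria (7.1 and SAP 3.1 repeat the rule). If exploration stops because they are met, the MTD is the previous dose. If they are still unmet at the highest dose, "the maximum tolerated dose is greater than or equal to the maximum escalation dose".

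**The concern.** The rule is stricter for less serious events. Two patients with severe but non-serious related events at one dose must open a discussion. Three patients at one dose who each needed help to recover from related hypoglycaemia need not.

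Two things are at stake. At a lower step, a cohort could move up after a severe related case without the discussion that 3.2.3 makes mandatory for other serious related events. At the top dose no step remains, so there the gap affects only the MTD statement, which could read as at least 6.0 mg despite related severe episodes at 6.0 mg. SAP 6.11 plans no data monitoring meetings that would fill the gap.

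**Working it through.** **The plan's own figures.** Three cohorts of 8 + 4 + 2 give 3 × 14 = 42, as stated in 9.2, with 8 IBI362 patients per cohort. The plan gives no operating characteristics for the stopping criteria, so there is nothing further to reproduce.

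**Each criterion applied to one related severe episode (8.3.4 definition).**

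| Criterion | Does the episode count? | Reason |
|---|---|---|
| 1 | No | Hypoglycaemia is named in the exemption, with no severity limit |
| 2 | Only if symptomatic with glucose < 3.0 mmol/L | Needs at least 4 patients at that dose level |
| 3 | No | Pancreatitis only |
| 4 | No | Non-serious events only; 8.3.4 makes the episode an SAE |

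**Counting cases at one dose level, with no other qualifying patients.**

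- Severe cases with glucose < 3.0 mmol/L: 1, 2 or 3 patients meet no criterion; 4 or more meet criterion 2.
- Severe cases without such a value: no number meets any criterion.

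**How many patients share a dose level.** The schedules are 1.0/2.0/3.0 mg (Cohort 1), 1.5/3.0/4.5 mg (Cohort 2) and 2.0/4.0/6.0 mg (Cohort 3). So 2.0 mg and 3.0 mg each occur in two cohorts, giving up to 8 + 8 = 16 IBI362 patients if counts are pooled. The doses 4.5 and 6.0 mg have 8. Section 3.2.3 does not say whether a dose level is pooled across cohorts. The threshold is 4 patients either way.

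**Illustration, on assumptions the documents do not supply.** Suppose s patients at a level of n have a documented severe episode, and each other patient independently has a milder related symptomatic event below 3.0 mmol/L with probability q. Criterion 2 is unmet if at most 3 − s of the other n − s patients qualify:

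P(no criterion met | s) = BinomCDF(3 − s; n − s, q)

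| n | s | q = 0% | q = 10% | q = 20% |
|---|---|---|---|---|
| 8 | 1 | 100% | 97.4% | 85.2% |
| 8 | 2 | 100% | 88.6% | 65.5% |
| 8 | 3 | 100% | 59.0% | 32.8% |
| 16 | 1 | 100% | – | 39.8% |
| 16 | 2 | 100% | – | 19.8% |

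Two entries written out at q = 20%, s = 1:

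- n = 8: 0.8^7 + 7(0.2)(0.8^6) + 21(0.2^2)(0.8^5) = 0.2097 + 0.3670 + 0.2753 = 0.852.
- n = 16: 0.8^15 + 15(0.2)(0.8^14) + 105(0.2^2)(0.8^13) = 0.0352 + 0.1319 + 0.2309 = 0.398.

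The q = 0% column only restates the rule. The spread between n = 8 and n = 16 shows how far any figure depends on the pooling assumption and on q.

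**The case against.** The strongest reply is that the four-patient rule is a deliberate, hypoglycaemia-specific choice, and that other safeguards do the work.

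- Protocol 4.4.1 lists a severe hypoglycaemic event as a reason to discontinue that patient's drug.
- The single-patient intolerance criteria after Table 1 already provide for a discussion with the sponsor.
- Hypoglycaemia is an AESI reported within 24 hours (8.3), and SAEs go to the sponsor within 24 hours and on to the ethics committee and regulators (8.7).
- The sponsor is unblinded (5.1.2), so a voluntary discussion may well take place.
- Patients take no glucose-lowering drug other than metformin and study drug, so the risk may be low.

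All of this stands and limits the practical harm. None of it enters the MTD rule or requires a cohort-level discussion.

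Three readings might bring other criteria into play:

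- **A serious sequel.** Section 8.6.3 has severe or serious secondary events recorded in their own right. An injury from a fall, for example, could meet criterion 1 unless it too is judged an expected pharmacological event. This stands, and is why the point is confined to the episode itself.
- **The general severity scale in 8.4.** On that scale an unassisted episode might be severe but non-serious and count under criterion 4. But 8.3.4 states how severity of hypoglycaemia is decided, and every episode severe by that definition is an SAE.
- **The word 'expected'.** The redacted risk section may say which events are expected, and an investigator might call a grave episode unexpected. However, 3.2.3 does not refer to that section, and it names hypoglycaemia without qualification.

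A reader might also infer that affected patients would go on being escalated, or that severe cases would stay hidden. The documents do not support either: 4.4.1 addresses the first, and SAP 6.6.1 tabulates and lists SAEs.

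**Conclusion.** The gap is real on the text. A related severe hypoglycaemic episode, as 8.3.4 defines it, can itself count only toward criterion 2. Fewer than 4 qualifying patients at a dose level, or any number of episodes without glucose below 3.0 mmol/L, require no cohort-level discussion, and the MTD can still be stated as at least the top dose.

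The conclusion rests on reading the exemption as written and on 8.3.4 governing the severity and seriousness of hypoglycaemia. It does not rest on an event rate, because the documents give none for severe episodes. It would be tempting to quote a probability that a severe case passes without a trigger. Any such figure is an assumption, and 4 of 8 is not the general denominator.

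Nor do the documents show that the gap affected this trial. Supplementary Table S3 reports hypoglycaemia as a treatment-emergent event in 2 of 24 IBI362 patients (1 + 0 + 1 across the groups; 2/24 = 8.3%), without stating severity.

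**What to change.** 1. Add to criterion 1, in 3.2.3 and the synopsis: *This exception does not apply to severe hypoglycaemia as defined in 8.3.4, with or without a glucose value.* One related severe case then opens the discussion.

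2. Add one line to the MTD rule in 2.2.1, 7.1 and SAP 3.1: *Where a criterion is met but the discussion does not stop escalation, or a criterion is met at the top dose, the MTD follows the documented outcome of that discussion and is reported with the triggering events.* Without this line, the first change would leave the MTD undefined in those cases, because the present rule covers only a stop after a criterion is met and criteria never met.

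The cost is two sentences. Meeting a criterion only opens a discussion, so no escalation stops automatically. The downside is that discussions may open more often and the MTD statement may be less favourable. If dosing is complete, the MTD statement can still be qualified in the report, and the wording corrected in later protocols.

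A separate, optional addition is a table of related severe and serious events by dose level. The primary endpoint is "the incidence and severity of adverse events at each dose level", whereas SAP 6.6.1 summarises by treatment group and each IBI362 group passes through three planned doses.

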## 4 Study Population

Deviations from eligibility criteria are not allowed because they may affect the scientific integrity of the study, regulatory acceptability, and/or patient safety. Therefore, patients must meet protocol-specified criteria.

### 4.1 Inclusion criteria

Patients will be included in the study if they met all of the following criteria:

1. A diagnosis of type 2 diabetes, as defined by WHO (1999) for at least 6 months.
2. Male or female, aged 18 to 75 years at signing informed consent.
3. Blood glucose will be inadequately controlled by lifestyle intervention alone or with stable dose of metformin ( $\geq 1000$  mg/day or maximum tolerated dose) within 2 months prior to screening.
4.  $7.5\% \leq \text{HbA1c} \leq 11.0\%$  by local laboratory at screening.
5.  $20 \leq \text{BMI} \leq 35$  kg/m^2 (BMI = weight (kg)/height (m^2)).
6. Maintain a stable diet and regular exercise lifestyle during the study.
7. Willing to sign the Informed Consent Form (ICF) and able to participate in the trial and comply with all trial requirements.

## 4.2 Exclusion Criteria

Patients will be excluded from the study if they met any of the following criteria:

1. Type 1 diabetes, gestational diabetes, or other types of diabetes.
2. Ketoacidosis or lactic acidosis within 6 months prior to screening.
3. History of severe hypoglycemic episodes within 6 months prior to screening, defined as symptoms of neuroglycopenia that require supportive care from others, or complete ignorance of hypoglycemia or lack of awareness of hypoglycemic symptoms. Patients who are unable to communicate and understand the symptoms of hypoglycemia and appropriate treatment should also be excluded from the trial at the discretion of the investigator.
4. Acute myocardial infarction, unstable angina pectoris, coronary artery bypass grafting, coronary intervention (except diagnostic angiography), transient ischemic attack (TIA), cerebrovascular accident, acute and chronic heart failure within 6 months before screening.
5. Abnormal 12-lead ECG (e.g., QTcF > 450 ms, PR interval < 120 ms, or PR interval > 220 ms, second-degree and third-degree atrioventricular block, ventricular conduction delay, i.e., QRS > 120 ms, right bundle branch block, left bundle branch block, Wolff-Parkinson-White syndrome) at screening that increase the risk of the patient or may cause confusion in the analysis of ECG data (QT); or taking any drug that may affect the QT interval at the discretion of the investigator, e.g., antiarrhythmic drugs class IA and III, cisapride, macrolide antibiotics and psychotropic drugs (phenothiazines [pyridazine, chlorpromazine, pyridazine], butyrophenones [droperidol, haloperidol] and loperamide).
6. Previous diagnosis of long QT syndrome.
7. Uncontrolled blood pressure at screening with systolic blood pressure > 140 mmHg or < 90 mmHg and diastolic blood pressure > 90 mmHg or < 50 mmHg.
8. Heart rate < 50 bpm or > 90 bpm at screening.
9. Active or untreated malignancy within 5 years prior to screening, or in clinical remission of malignancy (except for patients with basal and squamous cell carcinoma of the skin, carcinoma in situ of the cervix, and papillary thyroid carcinoma without postoperative recurrence).
10. Previous history of acute or chronic pancreatitis, or serum lipase/amylase > 2 × upper limit of normal at screening, or fasting triglycerides > 5.65 mmol/L (500 mg/dl). If the patient is on lipid-modifying therapy, the dose must be stable for 30 days prior to screening.
11. Clinically symptomatic liver disease, acute or chronic hepatitis, or transaminases (ALT and AST) and alkaline phosphatase (ALP) > 2 × upper limit of normal and total bilirubin > upper limit of normal at screening.

12. Calcitonin  $\geq 15$  ng/L at screening.
13. EGFR  $< 60$  mL/min/1.73 m^2 at screening, estimated using the modified MDRD formula:  $eGFR = 175 \times [(\text{serum creatinine } (\mu\text{mol/L})/88.4)]^{-1.234} \times [\text{age (years)}]^{-0.179} \times 0.79$  (female) or  $\times 1$  (male).
14. History or presence of psychiatric disorder at screening that would make participation in this study inappropriate at the discretion of the investigator.
15. Have Diagnosed of gastroparesis or received any form of obesity surgical procedure, or had abnormal gastric emptying considered clinically significant by the investigator.
16. Known history of regular drug abuse.
17. Positive human immunodeficiency virus (HIV) antibody and/or HIV infection at screening, or positive syphilis antibody.
18. History of hepatitis B and/or positive hepatitis B surface antigen at screening or positive hepatitis C (HCV) antibody at screening.
19. Previous diagnosis of Gilbert's syndrome.
20. International normalized ratio (INR) of prothrombin time greater than the upper limit of normal at screening.
21. History of medullary thyroid C-cell carcinoma, MEN (multiple endocrine neoplasia) syndrome 2A or 2B, or relevant family history.
22. Diagnosed with autonomic neuropathy, manifested as: urinary retention, resting tachycardia, orthostatic hypotension, and diabetic diarrhea.
23. Significant weight change with a percentage change  $> 5\%$  within 3 months prior to screening.
24. Donation of  $\geq 400$  mL of blood or excessive blood loss or bone marrow transplantation within 3 months before screening, or presence of hemoglobinopathy, hemolytic anemia, sickle cell anemia, or hemoglobin  $< 110$  g/L (men) or  $< 100$  g/L (women).
25. Hyperthyroidism or hypothyroidism confirmed by clinical assessment and/or TSH abnormality that, in the opinion of the investigator, may increase the risk of the patient.
26. Use of antidiabetic drugs other than metformin within 2 months prior to screening.
27. Use or planned to use weight-lowering medications such as Liraglutide, Orlistat, Sibutramine HCl, Phenylpropanolamine, Chlorphenindole, Phenylbutamine, Chlorocarbazon HCl, Fintramine, Fintramine/Topyrate, Bupropion, Naltrexone/Bupropion within 3 months prior to screening during the trial.
28. Chronic use of glucocorticoids (cumulative or continuous use  $> 2$  weeks) within 1 year before screening, or use of glucocorticoids (excluding topical, intraocular, intranasal, intra-articular, inhalation) within 4 weeks before screening.

29. Ongoing central nervous stimulant use (e.g., methylphenidate hydrochloride) at screening, with the exception of caffeinated beverages.
30. Known history of hypersensitivity to study drugs or drug components.
31. Participation in a clinical trial of any drug or medical device within 3 months prior to screening (randomized and received medication).
32. Female with childbearing potential, except those who are sterilized or amenorrheic, who are unwilling to inform their sexual partners of their participation in this clinical study and do not take effective contraceptive measures during the study. Male who are unwilling to inform their female sexual partners of the participation in the clinical study and unwilling to take effective contraceptive measures during the study.
33. Pregnant or lactating women or women who are preparing for pregnancy or breastfeeding during the study period
34. Any clinically significant abnormal laboratory value that may interfere with the interpretation of efficacy and safety data at the discretion of the investigator in this study.
35. Patients with any other factors that may affect their cooperation, efficacy, or safety evaluation at the discretion of the investigator, such as the presence of psychiatric disorders.
36. Average weekly alcohol intake of more than 21 units for men and 14 units for women, or unwillingness to stop drinking 24 hours before the day of medication and throughout the study (1 unit = 360 ml of beer, or 150 ml of red wine, or 45 ml of distilled spirits/liquor).

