#### **4.4 Patient Discontinuation/Withdrawal**

##### **4.4.1 Treatment discontinuation**

##### **1) Liver enzyme and other laboratory tests**

In any case, discontinuation of study drug should be considered after joint discussion of investigator and the sponsor;

When a patient has baseline ALT/AST < 1.5 × ULN:

- ALT or AST ≥ 5 × ULN

- ALT or AST  $\geq 4$ x ULN for more than 2 weeks
- ALT or AST  $\geq 3$ x ULN and TBL  $> 2$ x ULN or international normalized ratio (INR)  $\geq 1.5$
- ALT or AST  $\geq 3$ x ULN with symptoms of fatigue, nausea, vomiting, right upper quadrant pain/tenderness, fever, rash and/or eosinophilia ( $> 5\%$ )
- ALP  $> 3$ x ULN
- ALP  $\geq 2.5$  x ULN and TBL  $> 2$  x ULN
- ALP  $\geq 2.5$ x ULN with symptoms of fatigue, nausea, vomiting, right upper quadrant pain/tenderness, fever, rash and/or eosinophilia ( $> 5\%$ )

When a patient has baseline ALT/AST  $\geq 1.5$  x and  $< 2$  x ULN:

- ALT or AST  $\geq 4$  x baseline
- ALT or AST  $\geq 3$  x baseline for more than 2 weeks
- ALT or AST  $\geq 2$  x baseline and TBL  $> 2$  x ULN or international normalized ratio (INR)  $\geq 1.5$
- ALT or AST  $\geq 2$  x baseline with symptoms of fatigue, nausea, vomiting, right upper quadrant pain/tenderness, fever, rash, and/or eosinophilia ( $> 5\%$ )

Note: If the patient is found to have ALT/AST at screening, the baseline data will be collected at least 2 weeks apart.

- CK elevation  $> 5$ x ULN
  - Lipase and/or amylase  $\geq 3$  x ULN, the possibility of pancreatitis should be considered by the investigator (Table 5)
- 2) Hyperglycemia/hypoglycemia:
- The study drug should be discontinued due to deterioration in blood glucose control during the trial, fasting blood glucose  $> 13.3$  mmol/L with other excluded causes (e.g., increased blood glucose due to concurrent disease);
- The patient had a severe hypoglycemic event or persistent hypoglycemia (see section 8.3.4 for details);
- 3) The patient was inadvertently withdrawn from the study if the sponsor or investigator determined that the patient did not meet the enrollment criteria.
- #### 4.4.2 Withdrawal
- 1) Participation in other clinical trials during the trial is defined as signing the informed consent form for other trials;

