## **5.4 Administration During Pregnancy, Childbearing Age, or Lactation**

### **5.4.1 Pregnancy**

Women who are pregnant cannot be enrolled in this study. Subjects with childbearing potential must use the highly effective contraception

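### Exclusions 7 and 11 join their limits with 'and', so a single abnormal value escapes the fixed limits, and section 4.4.1 has no numeric liver rule for a baseline ALT/AST at or above 2 × ULN

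*Combined protocol and SAP*

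**What the plan says.** **How the list works.** Protocol section 4.2 opens with "Patients will be excluded from the study if they met any of the following criteria". One numbered criterion is therefore enough, and the connectors inside each criterion decide what it catches. Section 4 adds "Deviations from eligibility criteria are not allowed".

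**Exclusion 11.** After symptomatic liver disease and hepatitis, the numeric part is "transaminases (ALT and AST) and alkaline phosphatase (ALP) > 2 × upper limit of normal and total bilirubin > upper limit of normal".

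**Exclusion 7.** The limits are "systolic blood pressure > 140 mmHg or < 90 mmHg and diastolic blood pressure > 90 mmHg or < 50 mmHg".

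The synopsis repeats both wordings.

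**Section 4.4.1 (treatment discontinuation).** The liver criteria come in two sets. The first is headed "When a patient has baseline ALT/AST < 1.5 × ULN". The second covers a baseline from 1.5 up to, but not including, 2 × ULN. There is no third set.

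**Exclusion 32 (side note).** It applies to women "who are unwilling to inform their sexual partners of their participation in this clinical study and do not take effective contraceptive measures", and to men who are "unwilling to inform their female sexual partners of the participation in the clinical study and unwilling to take effective contraceptive measures". Section 5.4.1 says "Subjects with childbearing potential must use the highly effective contraception".

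**The concern.** An exclusion built from several limits joined by 'and' is met only when all of them are breached. For liver tests and blood pressure, one value far out of range is normally reason enough for a fixed limit to act. The neighbouring exclusion 10 does work that way: raised lipase/amylase and raised triglycerides are joined by 'or'.

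Section 4.4.1 makes this more than loose wording. Its two baseline sets stop below 2 × ULN, as if nobody could enter above that level, whereas exclusion 11 as written lets such patients through its numeric limits. The two sections do not describe the same population.

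Safety and tolerability are the primary endpoint, and elevated transaminases are an event of special interest (section 8.3). In a multicentre trial, sites may also read the connectors differently and admit different patients.

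**Working it through.** The documents give no figure to reproduce; this is a check of logic.

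**Step 1. Exclusion 11.** There are four components: ALT, AST and ALP (each > 2 × ULN) and total bilirubin (> ULN). Each is in or out of range, so 2^4 − 1 = 15 patterns have at least one component out of range.

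| Reading | Patterns excluded | ALT 5 × ULN only | ALT and AST 6 × ULN, ALP and bilirubin normal |
|---|---|---|---|
| All four limits required | 1 of 15 | not excluded | not excluded |
| Any enzyme, plus bilirubin | (2^3 − 1) × 1 = 7 of 15 | not excluded | not excluded |
| Each limit alone | 15 of 15 | excluded | excluded |

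The counts are patterns, not patients, so they are not probabilities. They show that neither of the two readings that keep an 'and' catches raised transaminases with normal ALP and bilirubin.

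**Step 2. Exclusion 7.** Two readings keep the 'and'. The grouped reading is (SBP > 140 or < 90) and (DBP > 90 or < 50). Under strict precedence, where 'and' binds before 'or', it is SBP > 140, or (SBP < 90 and DBP > 90), or DBP < 50.

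| SBP/DBP (mmHg) | Grouped | Strict precedence | Each limit alone |
|---|---|---|---|
| 170/85 | not excluded | excluded | excluded |
| 130/115 | not excluded | not excluded | excluded |
| 85/60 | not excluded | not excluded | excluded |
| 190/115 | excluded | excluded | excluded |

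The 170/85 example depends on grouping the limits. The 130/115 and 85/60 examples pass under both readings. With the limits grouped, 1 of the 3 abnormal patterns (systolic only, diastolic only, both) is excluded.

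**Step 3. Baseline ALT/AST against section 4.4.1.** I let the higher of ALT and AST place the patient, because the protocol does not say which one governs.

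| Baseline | Caught by no. 11 if all four are required | Caught if each limit acts alone | Set in 4.4.1 |
|---|---|---|---|
| 1.8 × ULN | no | no | 1.5 to < 2 |
| exactly 2 × ULN | no | no | none |
| 6 × ULN (ALP, bilirubin normal) | no | yes | none |

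With ALT and AST both at 6 × ULN, the gap does not depend on which enzyme governs. A value of exactly 2 × ULN is uncovered under every reading, because the exclusion says > 2 and the upper set says < 2.

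**Step 4. What the missing set leaves open.** Take a baseline of 5 × ULN. The first set's criterion of ALT or AST ≥ 5 × ULN would be met before any dose. The second set's criterion of ≥ 4 × baseline would be 4 × 5 = 20 × ULN. Neither set applies to this patient, and I propose neither; the distance between them shows how much is left to individual judgement.

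**Step 5. Size.** One patient in an IBI362 cohort of 8 is 1/8 = 12.5%.

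**The case against.** The strongest reply is that the protocol has other defences. Exclusion 34 lets the investigator exclude for a clinically significant abnormal laboratory value, and no. 35 for any other factor affecting safety evaluation. Using either is not a deviation. Exclusion 11 separately covers symptomatic liver disease and hepatitis; nos. 18 to 20 cover hepatitis B and C, Gilbert's syndrome and a raised INR. During treatment, elevated transaminases must be reported within 24 hours. Table 6 has a column for abnormal baseline liver tests. Section 4.4.1 begins with joint discussion between investigator and sponsor, and section 4.4.2 lets the investigator withdraw a patient for adverse events or where continuing is inappropriate.

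Much of this stands. A reader might infer that a patient with ALT 5 × ULN or 170/85 mmHg is simply eligible, or that there is no liver safety net. The documents support neither inference: the patient is not caught by the fixed limits, and what is missing is a numeric stopping criterion.

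The backstops are partial, however. Nos. 34 and 35 are discretionary, and no. 34 does not reach blood pressure. Table 6 governs reporting as a serious adverse event, not stopping. Its columns are defined by AST/ALT and bilirubin together, so a raised ALT with normal bilirubin fits neither clearly.

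It can also be said that the 'and' is a drafting or translation slip whose sense is recoverable from exclusion 10 and section 4.4.1. That is plausible, but the text stands in both the synopsis and 4.2.

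**Conclusion.** The point holds for exclusions 7 and 11. As written, their fixed limits miss patients with one component out of range. Section 4.4.1 has no numeric liver criterion for a baseline ALT/AST at or above 2 × ULN: neither of its two sets applies. This rests on the current text of 4.2, 4.4.1 and the synopsis, and for 170/85 mmHg on grouping the limits by pressure. The share of screened patients affected is unknown.

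Three further inferences should not be drawn.

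- **That only an 'or' between all components of no. 11 fits section 4.4.1.** The baseline sets there are defined by ALT/AST alone and put no baseline condition on ALP or bilirubin, so other readings fit equally well. Even the all-'or' reading leaves exactly 2 × ULN uncovered.
- **That such a patient would distort the safety summaries.** This is not shown. The laboratory table in SAP 6.6.2 crosses baseline with the worst later result, so an abnormal entry value appears as such. The blood pressure criteria in SAP Appendix 1 require a change from baseline as well as an absolute limit.
- **That exclusion 32 is a fault of the same weight.** It concerns behaviour, not a measured value. Inclusion 7 demands compliance with all trial requirements, and sections 5.4.1 and 5.4.2 require contraception. What remains is wording to be reconciled.

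**What to change.** 1. State the and/or logic of exclusions 7 and 11 explicitly, and identically, in the synopsis and in section 4.2.
2. Reconcile exclusion 11 with section 4.4.1 so that every baseline ALT/AST value that can be admitted, including exactly 2 × ULN, falls under a stated rule. Say which enzyme places the patient when ALT and AST fall in different ranges. The thresholds and the rule are for the sponsor to decide.
3. As a side note, reconcile the 'and' in exclusion 32, for women and men, with sections 5.4.1 and 5.4.2.

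The cost is a change of wording and, depending on the logic chosen, possibly a few more screen failures. Sample size and analysis are unaffected.
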